### Sample size

In the literature, an effect size of 0.62 has been described for mind-body therapies compared to no intervention in a group setting [29]. We assume a smaller effect size of 0.4 (Cohen’s d, baseline adjusted) for individual self-care relaxation exercise compared to usual care alone because individuals might be less focused and consequently less adherent in a self-care setting. To obtain a power of 80% using a 2-sided *t*-test with significance level of 0.05, 100 participants for each treatment group are needed (a total of 200 participants). We will include 110 participants per group (220 in total for each study) to compensate for dropouts.

### Data analyses

For each study, the primary analysis of the primary outcome (mean pain intensity over 3 months measured as the daily pain intensity on a NRS) will be performed using an analysis of covariance (ANCOVA) with a fixed factor of ‘treatment group’, adjusted for the baseline NRS value (fixed covariate). This will be used to test the null hypothesis of equal mean pain intensity between the two treatment groups. The analysis will be based on the full analysis set (FAS, all available data without imputation of missing values, based on the intention-to-treat principle) with a 2-sided significance level of 0.05. The results will be reported as adjusted group means with 95% confidence intervals and the *P-*value for the group comparison. All further analyses on the primary and all secondary outcomes will be considered explorative, and no adjustment for multiple testing will be performed. The secondary outcomes will be analyzed for the FAS similarly to the primary analysis depending on the scale and distribution of the data, that is ANCOVA, logistic regression, or Poisson regression, adjusted for the respective baseline value (when available). For the sensitivity analysis, the primary analysis of the primary outcome will be repeated based on the per-protocol population. In addition, missing data on the primary outcome will be imputed using multiple imputation techniques or other methods depending on the assumed missing data mechanism(s). In case of relevant differences in baseline variables between the treatment groups, the analysis of the primary outcome will be repeated with additional adjustment for these variables. As further supportive analysis, a mixed model for repeated measures (MMRM) will be fitted to compare the two treatment groups with respect to changes in the primary outcome over time. The model will include terms for treatment and time as fixed main effects, an interaction term for treatment by time, and the subject as a random effect, adjusted for the baseline value. The following subgroups will be considered for exploratory analyses: age groups, education (>10 years of school education, ≤10 years of school education), sex (male/female), severity of disease and duration of disease. Subgroup analyses will be performed on the primary outcome by including an interaction term (subgroup variable by treatment) in the main model, as well as by performing separate analyses for each subgroup. A detailed statistical analysis plan (SAP) will be developed prior to any data analyses. Data analysis will be performed in SAS version 9.3 or higher (SAS Inc., Cary, NC, USA).

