In these studies, the app will also be used as a tool for data collection. The content and the length of the electronic questionnaires and the diaries were chosen based on our previous experience with an app as a data collection tool in a study on menstrual pain [57]. Broad stakeholder involvement revealed that outcome measurements should be patient-relevant. It also indicated that app-delivered questionnaires can be provided more frequently than paper-pencil questionnaires as the completion of the questionnaires on smartphones requires less time [57]. Consequently, the app includes one daily question, short weekly diaries and two longer questionnaires only after the third and the sixth months. However, although we tried to minimize the number of outcome measurements, the valid tool for assessing pain acceptance [51] (after the third and sixth month) includes 20 questions and had to be implemented. Moreover, questionnaires adapted for app delivery are not yet validated and no data exists on whether the length or the frequency of electronic questionnaires influences the drop-out rates in randomized controlled trials.

We decided to measure pain intensity (NRS) daily and the average pain intensity over the previous 7 days was used to investigate whether there are differences between these 2 methods of pain assessment. This approach takes into account the consistent findings in pain assessment research that have shown that recall ratings of average pain might overestimate pain compared to ‘actual’ pain scores received from daily diaries [61–64], and it might minimize recall bias. Hence, the results of the study will add evidence to the ongoing discussion of the potential utility of recall ratings in pain clinical trials.

The main limitation of the study is that the patients will not be blinded, which might increase bias. It has been reported that bias due to lack of patient blinding is pronounced in complementary/alternative randomized clinical trials with patient-reported outcomes. However, the designed studies reflect a usual self-care setting and will provide evidence for a pragmatic self-care intervention that is easy to combine with care provided by medical professionals.

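### A month-6 ANCOVA of pain acceptance on available data would leave the month-3 score unused when month 6 is missing: some precision is lost, and bias is possible if loss depends on that score differently by arm

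*Protocol article*

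**What the plan says.** Table 1 of the protocol article schedules pain acceptance at baseline and after the third and sixth months. The Discussion confirms the two follow-up occasions: "the valid tool for assessing pain acceptance [51] (after the third and sixth month) includes 20 questions".

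Under Data analyses, the full analysis set is defined as "all available data without imputation of missing values", and the rule for secondary outcomes is: "The secondary outcomes will be analyzed for the FAS similarly to the primary analysis depending on the scale and distribution of the data". The models listed are ANCOVA, logistic regression and Poisson regression, each adjusted for the outcome's own baseline value where there is one. These are single-response models, and baseline is the only outcome history they use.

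The same section names two ways of handling incomplete follow-up and ties both to the primary outcome. One is a sensitivity analysis: "missing data on the primary outcome will be imputed using multiple imputation techniques or other methods". The other is a supportive mixed model for repeated measures (MMRM) for the primary outcome over time. All secondary analyses are declared explorative, and a detailed SAP is promised before any data are analysed.

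**The concern.** Someone who answers at month 3 but not at month 6 contributes nothing to an ANCOVA of month-6 acceptance, although the month-3 score is in the database and predicts the missing value. Two things follow. Information is discarded, so the standard error is larger than it needs to be. And the analysis rests on a stronger assumption than necessary: that month-6 loss is unrelated to the outcome given arm and baseline. A model using both visits also lets loss depend on the observed month-3 score.

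The setting makes that difference worth attention. Patients are unblinded, which the Discussion calls the main limitation. In the intervention arm the app is both the treatment and the only route for follow-up data, so a participant who gives up on the exercises may stop reporting too; a control participant has no treatment in the app to give up. The Discussion also notes that nothing is known about how the length or frequency of electronic questionnaires affects dropout. Loss that follows the month-3 score differently in the two arms is therefore plausible, though nothing in the article shows that it will occur.

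**Working it through.** **1. The plan's own figure.** Sample size section: d = 0.4, two-sided 0.05, 80% power. The normal approximation gives 2(1.960 + 0.842)²/0.4² = 2 × 7.851/0.16 = 98.1, so 99 per arm. The noncentral t gives power 0.7997 at 99 and 0.8036 at 100 per arm, so the stated 100 is reproduced. Raising 100 to 110 implies a dropout of 1 − 100/110 = 9.1%. That allowance was made for the primary outcome. No rate is given for pain acceptance at month 6, so 9.1% serves as the low end of a range.

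**2. Assumptions (not in the documents).** 110 per arm; SD 1; correlation 0.6 between baseline and each follow-up and 0.7 between months 3 and 6; month 3 complete; month-6 missingness m equal in both arms; true effect 0.30 SD.

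**3. Precision under random loss.** The partial correlation of months 3 and 6 given baseline is r = (0.7 − 0.36)/(1 − 0.36) = 0.531, so r² = 0.282. The available-case variance is proportional to 1/(1 − m). The joint model's variance is proportional to r² + (1 − r²)/(1 − m). Their ratio is 1 − m·r², so the saving is m·r²:

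- 9.1% missing: 2.6%
- 20%: 5.6%
- 30%: 8.5%
- 40%: 11.3%

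Simulated ratios were 0.92 to 0.94 at 25% missing and 0.88 to 0.89 at 40%, in agreement. The result depends on the correlations. With 0.5 to baseline and 0.5 between visits, r² = (0.25/0.75)² = 0.111, and the saving is 1.0% at 9.1% missing and 2.2% at 20%. With 0.5 and 0.8, r² = (0.55/0.75)² = 0.538, and it is 4.9% and 10.8%.

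**4. Bias when loss follows the month-3 score in the intervention arm only.** Loss is random in controls. The odds of leaving in the intervention arm are multiplied by 0.5 or 0.33 per SD better month-3 score. The standard error is √[2(1 − 0.36)/(110(1 − m))]. The rejection rate with no true effect can be approximated from b = bias/SE as Φ(−1.96 + b) + Φ(−1.96 − b), and compared with simulation.

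| Missing | Odds × | ANCOVA estimate (true 0.30) | SE | b | Null rejection, formula | Null rejection, simulated |
|---|---|---|---|---|---|---|
| 9.1% | 0.5 | 0.32 | 0.113 | 0.024/0.113 = 0.21 | 5.5% | 5.3–5.5% |
| 9.1% | 0.33 | 0.33 | 0.113 | 0.030/0.113 = 0.27 | 5.8% | 5.6% |
| 20% | 0.5 | 0.345 | 0.121 | 0.045/0.121 = 0.37 | 6.6% | 6.4–7% |
| 30% | 0.5 | 0.365 | 0.129 | 0.065/0.129 = 0.50 | 8.0% | 8% |
| 30% | 0.33 | 0.395–0.397 | 0.129 | 0.096/0.129 = 0.74 | 11.6% | 10.9–12% |

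The joint model, estimated from the same data, returned about 0.30 throughout.

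**5. Direction.** If improvers leave instead, the sign of the dependence flips and so, by symmetry, does the bias. The estimate becomes about 0.30 − 0.02 to 0.03 = 0.27 to 0.28 at 9.1% missing, and about 0.30 − 0.045 to 0.10 = 0.20 to 0.255 at 20–30%.

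**6. A second set of assumptions.** Correlation with baseline 0.5; between visits 0.5 to 0.8; true effect 0.40; log-odds of loss changing by 1 per SD.

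- Random loss, or loss depending on baseline only: ANCOVA gave 0.39 to 0.41, even with 20% missing in controls and 35% in the intervention arm.
- Same month-3 dependence in both arms: 0.37 to 0.43.
- Dependence in the intervention arm only: 0.42 to 0.45 at 9% missing, 0.44 to 0.54 at 20% or more.
- Joint model: 0.39 to 0.41 in every case.

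**The case against.** The strongest reply is that the target is partly inferred. The article does not say that months 3 and 6 are tested separately, nor which visit is the focus for pain acceptance. This stands as a limit: a separate month-6 ANCOVA is the natural reading of a single-response model applied to a two-visit outcome, but it is a reading.

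It can also be said that such detail belongs in the SAP. That is fair for covariance structures and similar matters. But the article is not silent: it assigns the secondary outcomes an analysis without imputation, and it names both remedies for the primary outcome only. A reader might infer that no other analysis of month-6 acceptance will ever be made. The article does not support that either, since the SAP is still to be written.

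Thirdly, a reader might infer that the month-6 comparison is biased, and biased in favour of the app. The documents do not support this. Bias needs month-6 loss to follow the month-3 score differently by arm, no section reports or predicts that, and the direction could be either. At the plan's own 9% allowance the bias is 0.02–0.03 SD against a standard error of 0.113. The larger figures need 20–30% loss and, at the extreme, a steep dependence.

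Finally, the outcome is explorative and baseline-adjusted available-case ANCOVA is a standard choice, so no confirmatory claim is at risk. That stands, and it limits the weight of the point. It is not a reason to prefer the analysis that uses less of the data.

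**Conclusion.** The point holds in conditional form. As written, the plan leads naturally to a month-6 comparison of pain acceptance that makes no use of month-3 scores from people missing at month 6. Under random loss the cost is about 1–5% of variance at 9% missing and about 6–12% at 20–40% missing, the latter with correlations of 0.6 and 0.7. Bias is a possibility, not a finding. In the scenarios examined it moves a true 0.30 SD by 0.02–0.03 at 9% missing (null rejection about 5.3–5.6%) and by 0.045–0.10 at 20–30% missing (about 6–12%). It vanishes if loss is random or depends only on arm and baseline. Correlations, missingness rates and dropout mechanism are all assumptions.

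Sick leave days follow the same schedule in Table 1, and a reader might extend the point to them. They may call for a count model, and no size has been worked out for them, so the conclusion is confined to pain acceptance. The primary analysis and the sample size are not affected. This is a minor improvement to an explorative analysis.

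**What to change.** In Data analyses, and then in the SAP, extend the repeated-measures approach already planned for the primary outcome to pain acceptance. Take the month-3 and month-6 scores as the two outcomes. Include treatment, visit, treatment-by-visit, baseline and baseline-by-visit, with an unstructured 2 × 2 covariance. Include everyone with at least one follow-up score, and report the adjusted treatment difference with its confidence interval at each month. Keep the available-case ANCOVA as the sensitivity analysis.

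The cost is a sentence or two of text and a few lines of SAS; no new data are needed. The model relies on data being missing at random given the observed scores, which is weaker than what the available-case ANCOVA requires but still an assumption. It recovers nothing for people missing at both follow-up visits.

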
### Ethics

The protocols of the studies were approved by the local ethics review boards at the Charité - Universitätsmedizin Berlin (approval number: Relaxback EA 1/260/13 and Relaxneck EA 1/259/13), and the studies will be conducted according to common standard guidelines for clinical trials (Declaration of Helsinki, and where it applies, the International Conference on Harmonization of Technical Requirements for Registration of Pharmaceuticals for Human Use and Good Clinical Practice (ICH-GCP) revised version, Somerset West, Republic of South Africa, 1996). All study participants will provide oral and written informed consent.

### Pragmatic explanatory continuum summary

From a methodological point of view, a study can be more focused on effectiveness or efficacy. ‘Effectiveness’ is defined as a measure of the extent to which an intervention, when deployed in the field in routine circumstances, does what it is intended to do for a specific population, whereas ‘efficacy’ refers to the extent to which a specific intervention is beneficial under ideal conditions [52]. The assessment of effectiveness in pragmatic trials can often be more relevant to policy evaluation and the health care decisions of providers and patients than the assessment of efficacy in explanatory trials [53]. Therefore, greater detail and transparency in reporting of the intervention characteristics, settings and assessment specifics are needed [54, 55]. The pragmatic explanatory continuum summary (PRECIS) [56] was developed to provide a graphical tool of ten design domains, which helps researchers categorize a trial’s focus as more pragmatic (effectiveness) or explanatory (efficacy). However, clinical studies are very often placed somewhere in the middle of the pragmatic-explanatory continuum [53, 57].

Three of the authors ([name], DP, SB) determined the placement of the study using PRECIS. The place of our trial in the pragmatic-explanatory continuum was defined more on the pragmatic side for the criteria of primary analysis, relaxation protocol, control protocol, eligibility criteria and outcome measurements, whereas participant compliance, follow-up intensity, and relaxation protocol were more on the explanatory side (Figure 1). Based on the ten PRECIS criteria, practitioner expertise and adherence were not applicable, so that 8 study design criteria remained.

**Figure 1 Fig1:**
[figure not shown]
**Pragmatic-explanatory continuum indicator summary (PRECIS) for the main study displaying the location of the eight study design criteria to be more on the pragmatic side (outer circles), more of the explanatory side (inner circles), or in the middle of the continuum.**

## Discussion

To the best of our knowledge, these are the first randomized pragmatic trials that will investigate whether app-delivered relaxations are an effective method to reduce chronic LBP or NP.

Chronic LBP and NP are common problems that constitute a large socioeconomic burden [4, 7, 58], and self-care therapies delivered by an App are easy to apply in a ‘real world setting’. Despite an increasing number of available pain related apps, very few of them have been tested for effectiveness [41]. Therefore, we planned both studies as pragmatic trials.

Due to the similar disease pattern of the two conditions, the intervention and study design is suitable for both patient groups, thus fewer resources than usual were necessary to conduct two parallel trials.

The involvement of relevant stakeholders contributed positively to the development process of the two study protocols. One important result of the stakeholder involvement was the reduction of the exercise duration from 20 to 15 minutes daily because the stakeholders suggested that long exercise time might be associated with difficulty following the recommended protocol: 15 minutes was considered the minimal daily exercise time that is necessary to achieve a treatment effect, especially outside of a group setting, and this length was chosen to improve patient adherence to the exercises. Adherence is a strong predictor of treatment success in patients with chronic LBP [59]. To support adherence, we implemented notifications in the app that can be individualized and remind the participants to perform the exercises. The selection of three different exercises to induce the relaxation response considers the individual’s expectations, beliefs and preferences [60] and contributes to a more personalized, patient-centered therapy.

In these studies, the app will also be used as a tool for data collection. The content and the length of the electronic questionnaires and the diaries were chosen based on our previous experience with an app as a data collection tool in a study on menstrual pain [57]. Broad stakeholder involvement revealed that outcome measurements should be patient-relevant. It also indicated that app-delivered questionnaires can be provided more frequently than paper-pencil questionnaires as the completion of the questionnaires on smartphones requires less time [57]. Consequently, the app includes one daily question, short weekly diaries and two longer questionnaires only after the third and the sixth months. However, although we tried to minimize the number of outcome measurements, the valid tool for assessing pain acceptance [51] (after the third and sixth month) includes 20 questions and had to be implemented. Moreover, questionnaires adapted for app delivery are not yet validated and no data exists on whether the length or the frequency of electronic questionnaires influences the drop-out rates in randomized controlled trials.

We decided to measure pain intensity (NRS) daily and the average pain intensity over the previous 7 days was used to investigate whether there are differences between these 2 methods of pain assessment. This approach takes into account the consistent findings in pain assessment research that have shown that recall ratings of average pain might overestimate pain compared to ‘actual’ pain scores received from daily diaries [61–64], and it might minimize recall bias. Hence, the results of the study will add evidence to the ongoing discussion of the potential utility of recall ratings in pain clinical trials.

The main limitation of the study is that the patients will not be blinded, which might increase bias. It has been reported that bias due to lack of patient blinding is pronounced in complementary/alternative randomized clinical trials with patient-reported outcomes. However, the designed studies reflect a usual self-care setting and will provide evidence for a pragmatic self-care intervention that is easy to combine with care provided by medical professionals.

### Trial status

Recruitment was started in March 2014.

## Abbreviations

Ancova: analysis of covariance
AT: autogenic training
App: smartphone application
EMG: electromyographic
FAS: full analysis set
LBP: low back pain
MMRM: mixed model for repeated measures
NP: neck pain
NRS: numeric rating scale
NSAIDs: nonsteroidal anti-inflammatory drugs
PMR: progressive muscle relaxation
PRECIS: pragmatic explanatory continuum summary
SAP: statistical analysis plan
RR: relaxation response.
